## Specific objectives:

1. To assess the base-line level health care service utilization of neonates who lived in selected study clusters in Sidama region in 2023 (base-line survey).
2. To determine whether a community-based capacity-building intervention (SiMaNeH trial) improves neonatal thermal care (measuring immediate skin-to-skin, thorough drying, head covering, and delayed bath) (Paper-II)
3. To asses the effect of a community-based capacity-building intervention (SiMaNeH trial) in improving timely initiation and exclusive breast-feeding rate during neonatal period in intervention group compared to control group (Paper-III).
4. To determine the effect of a community-based capacity-building intervention (SiMaNeH trial) in improving identification of sick neonates, and referral in the intervention group compared to controls (Paper IV).
5. To describe the cost-effectiveness of community-based capacity-building intervention to improve neonatal health care service utilization (Paper- V)

# Methods and materials

**Methods**

**Setting**

This trial research project will take place in rural areas of Sidama, a regional state in southern part of Ethiopia. Sidama became an autonomous regional state in 2020, separating from the former Southern Nations, Nationalities, and Peoples Regional State (SNNPRS) which is divided into four new regional states between 2020 and 2023. Sidama is situated approximately 400 kilometers south of Addis Ababa with an estimated population of about 4.6 million people in 2023. The capital of the regional state is Hawassa. Still, more than 80 percent of the population lives in rural areas, where agriculture is the primary economic activity and access to quality healthcare services is limited.

In 2018, an empirical study in one of the districts in Sidama showed that fertility was lower than reported from national estimates with crude birth rate of 22.8 births per 1000 population and total fertility rate of 2.9 children per woman. Furthermore, the population is transitioning to a low-mortality and low-fertility rate (19). However, the United Nations projected crude birth rate for Ethiopia is 30.6 births per 1000 population in 2024 (20), far higher than the empirical findings.

[figure not shown]

Figure 1: The map of the study area within Sidama regional State, Ethiopia.

Table 1: Background demographic and health service characteristics of study population

| Background | Intervention | Control | Remarks |
| --- | --- | --- | --- |
| Total population in 2024 | 84 347 | 87 830 |  |
| Expected births in 2024^x^ | 2 530 | 2 634 |  |
| Number of existing health centers | 7 | 8 | some overlaps |
| Number of Health Extension Workers | 37 | 35 |  |
| Number of Health Developments Team | 545 | 560 |  |
| Average distance to health centers | 5.3 km | 5,1 km |  |
| *Note: ^X^ = annual birth rate (3% of population) multiplied by population* | | | |

**Theoretical and conceptual frameworks:**

The trial will employ theoretical and conceptual frameworks, including the WHO-endorsed Participatory Learning and Action (PLA) model (21). The PLA will be used as a guiding model to be used by a team of community resource persons comprised of religious, administrative, and local social scheme leaders, and women support groups. The resource (support) group will use the model to identify, prioritize, address and re-plan based on previous achievements and weakness related to maternal and newborn care in their villages (22). In addition, the intervention will benefit from the process-based approaches of Theory of Change (TOC) principles (23). TOC model helps to understand and implement how activities, outcomes and impacts are connected to each other. Furthermore, WHO and Ethiopian Ministry of health principles of essential maternal and newborn care will be implemented (24, 25) to improve the continuum of care.

**Trial registration**

This trial is registered at Pan African Clinical Trial Registry and its number is PACTR202402782261294 and the link is <https://pactr.samrc.ac.za/TrialDisplay.aspx?TrialID=25464>

**Time Frame:**

| Table 2: Work plan for capacitating community health actors and other community groups in maternal continuum of care study |
| --- |

| **S/N** | **Activities** | **2021/2022 Academic Year** | | | | | | **2022/2023** | | | | **2023/ 2024** | | | | **2024/ 2025** | | | |
| --- | --- | --- | --- | --- | --- | --- | --- | --- | --- | --- | --- | --- | --- | --- | --- | --- | --- | --- | --- |
|  |  | **Sep- Nov** | **Dec - Feb** | **Mar -May** | | **Jun-Aug** | **Sep- Nov** | | **Dec - Feb** | **Ma -May** | **Jun-Aug** | **Sep- Nov** | **Dec - Feb** | **Ma -May** | **Jun-Aug** | **Sep- Nov** | **Dec - Feb** | **Ma -May** | **Jun-Aug** |
| 1. 1 | Developing final proposal |  |  | |  |  |  | |  |  |  |  |  |  |  |  |  |  |  |
| 1. 2 | Ethical issue secure |  |  |  | |  |  | |  |  |  |  |  |  |  |  |  |  |  |
| 1. 3 | Pilot Test tools |  |  |  | |  |  | |  |  |  |  |  |  |  |  |  |  |  |
| 1. 4 | Data collectors training |  |  |  | |  |  | |  |  |  |  |  |  |  |  |  |  |  |
| 1. 5 | Implementation of the Intervention |  |  |  | |  |  | |  |  |  |  |  |  |  |  |  |  |  |
| 1. 6 | Follow up |  |  |  | |  |  | |  |  |  |  |  |  |  |  |  |  |  |
| 1. 7 | Collecting data |  |  |  | |  |  | |  |  |  |  |  |  |  |  |  |  |  |
| 1. 8 | Data analysis |  |  |  | |  |  | |  |  |  |  |  |  |  |  |  |  |  |
| 1. 9 | Writing First draft report |  |  |  | |  |  | |  |  |  |  |  |  |  |  |  |  |  |
| 1. 10 | Writing Final Report |  |  |  | |  |  | |  |  |  |  |  |  |  |  |  |  |  |
| 1. 11 | Attending conference internationally |  |  |  | |  |  | |  |  |  |  |  |  |  |  |  |  |  |
| 1. 12 | Presentation of findings |  |  |  | |  |  | |  |  |  |  |  |  |  |  |  |  |  |
| 1. 13 | Submitting the final report |  |  |  | |  |  | |  |  |  |  |  |  |  |  |  |  |  |
| 1. 14 | Manuscript writing and sending for journals |  |  |  | |  |  | |  |  |  |  |  |  |  |  |  |  |  |
| 1. 15 | Final dissertation report |  |  |  | |  |  | |  |  |  |  |  |  |  |  |  |  |  |

**Ethical approval**

The study was approved by the institutional review board (IRB) of Hawassa University in Ethiopia (IRB/363/15) issued on August 07/2023. Permission for the study was received from Sidama Regional State Health Bureau and subsequent local authorities. All participants will be asked to give a written consent information sheet to be presented to them and attached with this protocol. Participants will be informed of the aim of the study and their freedom to refuse or participate and withdraw from the trial freely.

**Study design**

This study will use a cluster randomized controlled trial with two arms of equal size. We use villages (kebeles in Ethiopian structure) with an average population of about 5,000 people as the clusters served as units of randomization.

**Randomization technique and Blinding**

We selected 20 clusters randomly from eligible 80 from four districts in the region and allocated them into intervention and control in 1:1 allocation,10 each to the intervention and control cluster. To balance based on the distance of clusters from nearby health facilities between intervention and control clusters, we used stratified first the 20 clusters into four categories based on the population size and distance to the nearest health facility to reduce confounding. The four strata were: 1) Higher population (over 4,000 residents) and longer distance (more than an hour of walking distance), 2) Higher population and shorter distance (less than an hour walking distance 3) Lower population (less 4,000 residents) and shorter distance and 4) Lower population and longer distance. Then clusters from each stratum were randomly allocated to intervention and control using a computer-generated random number using simple randomization. A seed number was produced and sent from a university of Bergen as a starting point for random number generation. Blinding is difficult because of the nature of cluster randomized trials, but we created a buffer zone between intervention and control clusters to reduce intervention contamination. Data collectors are independent of the intervention process and do not have formal information on which study arm the cluster to which they collect data belongs.

**Sampling strategy and sample size**

To calculate the sample size of the participating mothers and babies in the study, we used the sample size calculation for cluster randomized controlled trials with the fixed number of clusters recommended by Karla Hemming and colleagues (26). We fixed the number of clusters to 20 for logistic and access reasons. We base our estimate of pregnant women with annual crude birth rate of 30 births per 1000 population per United Nations Population Division projection for Ethiopia in 2024 (20). The average pregnant mother-baby pair per cluster was estimated to be 150 during the study period. To estimate the minimum required sample, the trial aims to increase the completion rate of the continuum of pregnancy, birth, and postpartum care from an estimated 20% exiting status to 30% in intervention clusters with a 95% significance level and 80% power. We take the intra-cluster correlation of 0.01. Substituting these numbers in the following formula gives the minimum number of mother-baby pairs for the study. We used the following formula to calculate the sample size.

$$n=\frac{\left( Z\alpha/2+Z\beta\right)^{2}\times\left( p1\left( 1-p1 \right)+p2\left( 1-p2 \right) \right)}{\left( p1-p2 \right)^{2}} \times\left( 1+m-1 \right) \times ICC$$

- *n* is the sample size = number of pregnant mother-baby pairs needed per study arm
- *Z_α/2_* is the z-value corresponding to the significance level (α=0.05, Zα/2 =1.96).
- *Z_β_* is the z-value corresponding to the desired power (β = 0.20, Zβ = 0.84).
- *p_1_* is the expected proportion in the control group (0.20), the continuum of care completion in control clusters.
- *p_2_* is the expected proportion in the intervention group (0.30), expected continuum of care completion in intervention clusters.
- *m* is the average cluster size = 150 mothers per cluster on average.
- *ICC* is the intra-cluster correlation coefficient (0.01).

This provides a minimum of 723 pregnant women-baby pairs per trial arm, resulting in a total sample size of 1446. However, because several outcome measures may need more samples and to have adequate numbers for sub-analysis, we decided to recruit a total of 2000 woman-baby pairs, 1000 in each arm.

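### The sample-size paragraph does not describe the planned trial: misprinted formula, a cluster size of 150 that is not the one recruited, and no term for the 20 fixed clusters

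*Protocol*

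**What the plan says.** Protocol, Sampling strategy and sample size:

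- Method: "we used the sample size calculation for cluster randomized controlled trials with the fixed number of clusters", with the number of clusters fixed at 20.
- Target: completion of the continuum of care is to rise "from an estimated 20% exiting status to 30% in intervention clusters with a 95% significance level and 80% power". The legend gives z = 1.96 and z = 0.84, and the ICC is set at 0.01 without a source.
- Cluster size: m "is the average cluster size = 150 mothers per cluster on average".
- Formula: the usual two-proportion expression, multiplied by a last factor printed as (1 + m − 1) × ICC. The number of clusters does not appear in it.
- Result: "This provides a minimum of 723 pregnant women-baby pairs per trial arm, resulting in a total sample size of 1446". Recruitment is then raised to 1,000 per arm, to serve other outcomes and sub-analyses.

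Two other places bear on the inputs. Randomization technique and Blinding allocates 10 clusters to each arm. Study design describes clusters "with an average population of about 5,000 people", whereas Table 1 under Setting gives "Total population in 2024 | 84 347 | 87 830" for the two arms.

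**The concern.** This is the only justification of the sample size for the primary outcome, and its parts do not fit together. The printed formula does not return the printed result. The cluster size in the formula cannot be obtained from the planned numbers. The method named is not the one shown. A reader therefore cannot reproduce the minimum from the text, and cannot learn from it what power 10 clusters of 100 women per arm provide. Power is the property that matters once the number of clusters is fixed, and it depends strongly on the ICC.

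**Working it through.** **Inputs (Sampling strategy and sample size, unless noted).** p1 = 0.20, p2 = 0.30, z = 1.96 and 0.84, ICC = 0.01, m = 150. Clusters per arm k = 10 (Randomization technique and Blinding). Recruitment is 1,000 per arm.

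**1. Reproducing 723.**
- Individually randomised base: (1.96 + 0.84)² × (0.16 + 0.21) / 0.10² = 7.84 × 0.37 / 0.01 = 290.08 per arm.
- Standard design effect: 1 + (m − 1) × ICC = 1 + 149 × 0.01 = 2.49.
- 290.08 × 2.49 = 722.3, rounded up to 723. The protocol's figure is reproduced.

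**2. The formula as printed.** (1 + m − 1) × ICC = 150 × 0.01 = 1.50, and 290.08 × 1.50 = 435.1. The printed expression contradicts the 723 beneath it.

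**3. The cluster size.**
- 723 / 10 = 72.3 women per cluster; 1,000 / 10 = 100.
- At 150 per cluster, 723 women would fill 723 / 150 = 4.8 clusters per arm, not 10.
- Design effects for the sizes that can occur: 1 + 71.3 × 0.01 = 1.71 at 72.3, and 1 + 99 × 0.01 = 1.99 at 100. With m = 100 the same formula needs 290.08 × 1.99 = 577.3, so 578 per arm.

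**4. A calculation that uses the fixed number of clusters.** Setting m = n/k and solving for n:
- n = 290.08 × k × (1 − ICC) / (k − 290.08 × ICC) = 290.08 × 10 × 0.99 / (10 − 2.9008) = 404.5. That is about 405 per arm, or 41 women per cluster, with z-values.
- With a t reference on 18 df (20 clusters − 2), 405 per arm gives about 0.755 power. About 48 per cluster are needed for 0.80.

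**5. Power with 10 clusters per arm.** SE = √(0.37 × DE / n), noncentrality 0.10 / SE, two-sided 0.05, t on 18 df. At ICC 0.01:

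| n per arm | DE | SE | 0.10/SE | Power |
|---|---|---|---|---|
| 723 | 1.71 | 0.0296 | 3.38 | 0.89 |
| 1,000 | 1.99 | 0.0271 | 3.69 | 0.94 |

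With a normal reference the powers are about 0.92 and 0.96.

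**6. Sensitivity to the ICC.** The range is an assumption; the protocol gives only 0.01.

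| ICC | 723 per arm | 1,000 per arm |
|---|---|---|
| 0.01 | 0.89 | 0.94 |
| 0.02 | 0.77 | 0.81 |
| 0.03 | 0.66 | 0.69 |
| 0.05 | 0.50 | 0.52 |

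Power of 0.80 holds up to an ICC of about 0.017 at 723 per arm and about 0.021 at 1,000 per arm.

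**7. Population per cluster.** (84,347 + 87,830) / 20 = 172,177 / 20 = 8,609, against about 5,000 in Study design. At the 3% birth rate used in Table 1 this is about 258 births per cluster per year. 5,000 × 0.03 = 150 matches the m used, but the protocol ties its 150 only to the study period, so that origin is an inference. Step 3 does not depend on it.

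**The case against.** The best defence is that nothing of substance went wrong. The correct design effect was evidently computed and its brackets were then misplaced in typesetting; correcting them leaves 723 unchanged. Using 150 instead of 72 or 100 overstates the design effect, so the stated minimum is larger than needed, and the trial recruits more still. On the protocol's assumptions power exceeds 80% at both sizes, and no participant number or analysis changes. All of this stands, and it limits the severity.

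Three stronger readings are tempting, and the protocol does not support them:

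- **That the requirement is really 435, or that 723 is a miscalculation.** It is not: 723 follows exactly from the design effect of 2.49.
- **That the increase to 1,000 is presented as securing the power.** The protocol justifies it by other outcomes and sub-analyses and makes no such claim. Nor are extra women useless at a higher ICC: at 0.02 they lift power from 0.77 to 0.81, although at 0.05 the gain is only from 0.50 to 0.52.
- **That the trial is underpowered.** Every figure well below 80% rests on an ICC that the protocol does not state. The missing source for 0.01 is a reporting gap, not evidence that 0.01 is wrong.

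What the defence does not remove is that the formula, the cluster size and the named method each disagree with the reported number or with the design.

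**Conclusion.** The point holds as a correction of stated figures, of moderate severity. The printed factor gives 435 beside a reported 723. The m of 150 matches neither 72 nor 100 women per cluster. The claimed fixed-cluster calculation is not the one shown. The pairing of 723 per arm with 80% power therefore does not describe 10 clusters per arm. The direction is conservative: at 20% versus 30% and ICC 0.01, power is about 0.89 at 723 and 0.94 at 1,000 per arm. These values assume equal cluster sizes, analysis of every woman recruited, and a t reference on 18 df that ignores the allocation strata. The 80% target holds at 1,000 per arm only up to an ICC of about 0.02, so the power statement should be conditional on the ICC.

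**What to change.** Rewrite the sample-size paragraph, leaving enrolment as it is:

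1. Print the inflation factor as [1 + (m − 1) × ICC].
2. Use m = 100 (design effect 1.99), or give the fixed-cluster formula with 10 clusters per arm: about 41 women per cluster with z-values, about 48 with a t reference on 18 df. Name whichever method is used.
3. Replace 723/1,446 for 80% power by the power of the actual 20 × 100 design: about 0.94 at ICC 0.01.
4. Add one sentence on sensitivity to the ICC, labelled as an assumed range (0.81, 0.69 and 0.52 at 0.02, 0.03 and 0.05), and state where 0.01 comes from. If the planned baseline survey is used to estimate the ICC, note that its maternal objective measures postnatal care within 48 hours, whereas the trial composite requires four postnatal contacts. It would therefore be the ICC of a different outcome.
5. Reconcile the cluster population of about 5,000 in Study design with the roughly 8,600 implied by Table 1.

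The cost is one paragraph of text and one population figure. The only change in substance is that the stated power becomes that of the real design and depends openly on the ICC.

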**Participants:**

**Inclusion criteria:**

We shall include mothers who permanently reside in the study clusters and consent to participate. All pregnant mothers who fulfill the above criteria and do not meet the following exclusion criteria will participate. This includes mothers in their gestational period of between the 20th and 26th weeks within the four months of the recruitment period (June-September 2024).

**Exclusion criteria:** We will not recruit mothers with less 20th weeks of gestation because of longer time needed for follow-up. In addition, mothers whose pregnancy terminated before 20th week of gestation will not be included because the main emphasis of the study is on completion of maternal care and utilization of newborn care. Mothers who do not consent to participate in the study after information will not be included.

**Intervention**

To achieve the aim of improving the completion rate of the continuum of essential care from pregnancy care through postnatal care, the intervention package uses four mechanisms of action to help reduce barriers to essential healthcare utilization. The four mechanisms of action are: 1) Actively identify and connect to healthcare services, 2) Educate and prepare at home, 2) Support emotionally and materially through local collective efforts, and 4) Provide home-based essential care in case when care from health facilities is not actual.

To implement the four mechanisms of action stated above, the project coordinates the efforts of three existing community health stakeholder groups through training and supervision. The three stakeholders are the community health workers (HEWs in Ethiopia), the women support groups (HDTs in Ethiopia), and the community resources groups, also termed community opinion leaders (COLs).

HEWs are women permanently employed on average two in all clusters (Kebeles) in Ethiopia and paid monthly salary from the government. They have overall responsibility in their clusters for health promotion, disease prevention, and provision of basic maternal and newborn care such as antenatal, postnatal, and baby resuscitation. HEWs will participate majorly in three of the four mechanisms of action, namely identification, educating and preparing, and provision of home-based essential care when delivery happens at home, in addition to routine postnatal care. Furthermore, they will coordinate the work of COLs for the local collective support efforts.

WDTs are about 30 voluntary groups of women in each cluster residing in sub-villages of clusters in Ethiopia, freely helping the works of HEWs. They have recognition from the government without getting paid. Because of their unique position closer to sub-villages, they have the unique opportunity to identify mothers as they become pregnant in their respective villages and connect to healthcare services. They also educate and prepare mothers and families for standard and emergency care. WDTs' main contribution to the intervention is actively identifying and connecting mothers and babies to essential standard care and emergency care when they observe danger signs. WDTs will give particular attention to high-risk and hard-to-reach mothers and newborn babies such as extremely poor, living in difficult topography and distant villages from the health facilities and HEWs stations as well as those with existing sicknesses and malnutrition. As such, the contribution of the village WDTs in the four mechanisms of action will be identifying and connecting, education and preparing and involving with COLs in strengthening financial, transport, and family care support through collective local efforts so that a mother or baby reaches to health facility and receives care.

Community opinion leaders (COLs) are key leaders who lead opinions such as approval of the importance of receiving healthcare services and coordinating local collective help mechanisms. COLs are a group of local leaders forming a committee which includes influential religious leaders, cultural leaders, local government administrative leaders, and leaders of local welfare scheme called IDIR in Ethiopia. IDIR is a local welfare system where families contribute financially or materially every month. This welfare system often shares serious costs during deaths and severe sicknesses.

The main responsibility of the COLs is identifying problem such as barriers hindering mothers and babies receiving important health care and fall out of the continuum of care. They respond to the problem coordinating local collective efforts, for example transport or financial support to reach a health facility and taking care of the family members at home. For this contribution, they meet every two-weeks to evaluate and re-plan their actions based on the principles of Participatory Learning and Action (PLA) model (21). WDTs help COLs with gathering and providing sub-village information. COLs use their high level of acceptance to visit and support families where the relationship between the woman and her husband is not smooth and put great pressure on the health and wellbeing of women or their newborns. At such households, COLs provide essential advice on the importance of care for a pregnant women and newborn babies. This is expected to contribute to a mother and baby receive essential care that improve their survival and wellbeing.

The project provides training and supervision support to the three key stakeholders participating in intervention.

For COLs, the training and supervision will be based on PLA model of problem identification, providing local solutions, evaluating the effect, and re-planning process. COLs receive a day-long initial training and a two-monthly supervision discussion for an hour during the project period.

Trainings and supervision to HEWs will have two dimensions: On one hand, HEWs will be trained and supported on technical refresher issues related to baby resuscitation and home-based immediate support when a birth occurs at home, and essential postnatal maternal and newborn care and on the other hand, they will be trained on leadership role to lead the efforts of COLs and WDTs. HEWs receive two days of intensive training followed by two-monthly supervision and monitoring meetings with the project team.

The training and supervision of WDTs will be mainly on identifying and connecting mothers and babies for normal essential care as well as detecting danger signs and referring for emergency care babies and mothers with severe sickness (danger signs). In addition, WDTs receive training on maternal essential self-care, preparation for healthcare, nutrition, rest, hygiene, and other important information which in turn they will teach mothers and families. Further, the WDTs receive training on tracking and giving special attention to high-risk mothers and babies in difficult families and hard-to-reach villages so that they are not left out or fall out of the critically needed healthcare services. Through these mechanisms, the project builds a supportive network around mothers to help improve the initiation and completion of essential services in the continuum of care around pregnancy and childbirth. Table 2 below describes the roles of each stakeholder to the four mechanisms of actions to improve continuum of care in the intervention clusters.

Table 2: The role of stakeholders in the community-based actions in intervention clusters

|  | 1. Identify and connect | 1. Educate and prepare | 1. Support through collective efforts | 1. Home-based essential care |
| --- | --- | --- | --- | --- |
| HEWs | All pregnant mothers for essential ANC, delivery, and postnatal care in collaboration with HDTs and COLs  Mothers and babies in high-risk of falling out of care, or even do not initiate first contact.  Screen and recruit mothers for study 20-26^th^ week of gestation. | Mothers and families on essential care, nutrition, hygiene…  Prepare mothers and family for facility delivery, emergency health seeking. | Mainly through coordinating the efforts of COLs | Encourage antenatal care as per the guidelines of MoH  Emergency maternal and newborn help for deliveries occurred at home.  Routine postnatal care for mothers and babies. |
| HDTs | Identify mothers and babies in her sub-village and connect to HEWs, COLs and health care.  Guide data collectors to locate homes. | Educate and prepare mothers and families on essential care, nutrition, hygiene, emergency care | Inform to COL s and HEWs about mothers and babies not receiving care | Educate and prepare.  Do not provide any technical care. |
| COLs | Identify mothers and babies at high-risk and hard-to-reach villages.  Identify mothers and babies in families with non-smooth relationships and in dangers.  Connect those identified to healthcare service. | Approve and promote the importance of essential health care.  Make PLA discussion to prepare for support when needed. | Facilitate finance, transport, and family care coordinating local collective efforts.  Continuously monitor their support provision | Make home visits to difficult families and provide advice and emotional support. |
| *Note: HEWs = Health extension workers, HDTs = Health development team, COLs = Community opinion leaders (religious, cultural, local welfare scheme, and administrative leaders working as a group to ensure support mechanisms), PLA = Participatory Learning and Action (a community problem solving model)* | | | | |

